### 2.7. Randomization and Allocation

After meeting the inclusion criteria, 70 qualified participants are being randomly allocated to either the PRP group and the HA group in a 1 : 1 allotment proportion. The irregular grouping sequence is performed concurring to an irregular list of numbers produced by the randomization center of Ningxia Medical University. It is hidden in an opaque sealed envelope.

The random sequence is overseen by particular personnel who have no contact with participants and are not included in the information collection or analysis. All qualified participants receive the following administrations free of charge, assessment, X-ray examination, health education, and quadriceps femoral training (both HA group and PRP group). All participants are strongly advised to follow up all evaluation and treatment plans as much as possible.

### 2.8. Blinding

The grouping of participants is unknown to the result evaluators, information supervisors, and statistical analysts. However, participants are not blinded since each participant is aware of their assigned group after allocation is complete. The evaluation progress is kept secret from the physiotherapists and participants in order to ensure the precision of the test indicators and guarantee the objectivity and reliability of the assessment.

Blinding is maintained throughout the entirety of the research process. After completion of the statistical investigation, the blind code will be unveiled.

### 2.9. PRP Injection Method

The patient is in the supine position with the affected knee flexion: 70°–80° and the feet in the neutral position. For local disinfection, the lower edge of the patella and 1 cm inside and outside of the patellar ligament (internal and external genicus) are selected as puncture points, which are used alternately. A disposable syringe is used to puncture into the joint cavity and 5 ml of the preprepared autogenous PRP is injected. If the joint effusion is present, the effusion is extracted first. After injection, the knee joint undergoes exercise on a passive range of motion and is observed for 20–30 minutes to determine that the subjects have no discomfort. For the first two days, participants are asked to do some light physical activity, limit weight on the affected lower limbs, and use ice packs for 10 minutes every eight hours a day. For mild to moderate pains, a maximum of four 500 mg acetaminophen tablets is permitted, and acetaminophen plus codeine is recommended if/when the pain persisted. With the exception of these painkillers, other drugs are not permitted for up to five days after injection. PRP joint injection is performed once a week for a total of 4 times.

### 2.10. Sodium Hyaluronate Treatment Group

The injection method is the same as that in the PRP test group, and patients are injected with 20 ml of sodium hyaluronate at a time at the joint (produced by Shanghai Baijia One Pharmaceutical Co. Ltd.). Hyaluronic acid is injected once a week, and the clinical efficacy is observed after 4 injections. The researchers give similar guidance and support to both groups.

### 2.11. Quadriceps Muscle Training

All patients begin quadriceps muscle training 24 hours after the intervention, and the training is conducted under the guidance of the therapist. Before each treatment, the preparatory activities, mainly including lower limb active exercise and knee flexor and extension exercise, is conducted for 3–5 minutes. Quadriceps femoral training method: (1) Isometric training: squat training: the patients position the back against the wall with the body straight and feet slightly wider than the shoulders. With toes facing front, the patients slowly squat using both legs for a duration of 2–5 minutes and a total of 5–10 times. Participants must make sure they stand slowly and rest for 5–10 seconds between each squat. (2) Isotonic training: a quadriceps training chair is used for this exercise. The patients take the sitting position and refrain from moving their legs whilst stretching and bending their knee 10 times each for 1 group. There are a total of 6 groups for each training session, with a rest period of 2 minutes between groups. Weight training is also carried out base on standard according to the patient's muscle strength. The weight is gradually increased until the patient can complete the required training volume. The above quadriceps muscle training lasts for 20 minutes each time, once a day, for a total of three times a week. Quadriceps muscle training is ongoing with the whole study process and requires the subjects to keep exercising consistently outside the hospital.

All results are assessed by experienced evaluators who have been trained and specifically allocated to manage these evaluations. Results are randomized blind in accordance after each of the standard visits. Each patient is evaluated by the same evaluator for every stage of the evaluation.

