## Abstract

Knee osteoarthritis is a common chronic degenerative joint disease in middle-aged and elderly people. Intra-articular injection for the treatment of knee osteoarthritis is a regularly utilized nonsurgical treatment in modern medicine. Hyaluronic acid (HA) and platelet-rich plasma (PRP) are two frequently employed intra-articular devices. Hyaluronic acid (HA) is an accepted nonsurgical treatment for symptomatic KOA, and platelet-rich plasma is a popular option in the treatment of KOA in recent years. The purpose of this research is to compare the efficacy and safety of intra-articular injection of platelet-rich plasma (PRP) versus hyaluronic acid (HA) on the pain score scale, knee function, and related inflammatory biomarkers in KOA patients using a clinical randomized controlled trial. Participants are being randomized into either the hyaluronic acid (HA) or into the platelet-rich plasma (PRP) group. All patients receive 4 weeks of treatment (once a week), and well-being support and quadriceps training (3 times a week). The primary outcomes are measured using the Western Ontario and McMaster Universities Osteoarthritis Index (WOMAC) and the visual analog scale (VAS). The secondary outcomes include the activities of daily living score, erythrocyte sedimentation rate, C-reactive protein testing, interleukin-6 levels, and X-ray examination. In order to monitor the occurrence of irregularities and abnormalities, patients are assessed at each visit, and restorative treatment is given if necessary. The results of this clinical trial will verify the efficacy of PRP and HA in the treatment of KOA and provide important evidence for the clinical treatment of KOA. The trial was enlisted at the Chinese Clinical Trial Registry on 26 September 2020 (ChiCTR2000038635).

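### Section 2.11 starts training with wall squats 24 hours after injection, inside the two days for which 2.9 asks for light activity and limited loading of the leg

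*Protocol article*

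**What the plan says.** Aftercare is set in section 2.9, under the PRP heading: "For the first two days, participants are asked to do some light physical activity, limit weight on the affected lower limbs". PRP is injected weekly, four times.

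For HA, section 2.10 says "The injection method is the same as that in the PRP test group" and "The researchers give similar guidance and support to both groups". HA is also given weekly for four injections. Section 2.10 does not itself repeat the two-day advice.

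The exercise programme is in section 2.11: "All patients begin quadriceps muscle training 24 hours after the intervention, and the training is conducted under the guidance of the therapist". After a short warm-up, patients do wall squats: "slowly squat using both legs for a duration of 2–5 minutes and a total of 5–10 times". They then do seated knee extension and flexion on a training chair. The section adds: "Weight training is also carried out base on standard according to the patient's muscle strength", with the weight raised step by step. On frequency it says: "The above quadriceps muscle training lasts for 20 minutes each time, once a day, for a total of three times a week". Training continues for the whole study. The Abstract likewise describes the weekly injections and the thrice-weekly training together.

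**The concern.** Two printed instructions cover the same hours and point in different directions. A therapist who follows 2.11 may have the participant doing wall squats one day after injection. A participant who follows 2.9 should still be sparing that leg. Nothing in 2.11 lightens the first session, and load is set by muscle strength, not by time since injection.

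What is at stake is the protocol's own precaution for a freshly injected knee. In addition, the precaution is written only under PRP, so a reader must infer whether HA participants receive the same aftercare.

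**Working it through.** The plan gives no figure on this point to reproduce. The check is an overlap of time intervals.

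**Inputs**
- Restriction: the first two days after injection, taken as 0–48 h (2.9).
- Training start: 24 h after the intervention (2.11).
- Injections: four, weekly, so at 0, 168, 336 and 504 h (2.9, 2.10).
- Training: three sessions a week, throughout the study (2.11).
- Participants: 70, allocated 1:1, so 35 per arm (2.1, 2.2).

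**Step 1. Window fixed by the start rule.** Overlap = 48 − 24 = 24 h. This holds whether the intervention means the first injection or the whole course, because either way training begins 24 h after an injection. The first injection is the likelier meaning, since the Abstract and 2.11 run training alongside the injections. If two days means the injection day and the next calendar day, the overlap is shorter than 24 h but not zero.

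**Step 2. Windows permitted over the course.** The two-day advice recurs with each injection.

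| Reading of the start rule | Windows per participant | Overlap |
|---|---|---|
| 24 h after the first injection, then continuous | 4 | 24 + 48 + 48 + 48 = 168 h |
| 24 h after each injection | 4 | 4 × 24 = 96 h |
| 24 h after the fourth injection | 1 | 24 h |

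These are hours in which 2.11 allows training while 2.9 advises against loading. They do not count sessions. Three sessions a week can all be placed outside the 48 h after injections 2 to 4.

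**Step 3. Counts across the trial.**
- Fixed by the start rule: 35 × 1 = 35 windows (PRP), or 70 × 1 = 70 if the advice covers HA.
- Permitted at most: 35 × 4 = 140 (PRP), or 70 × 4 = 280 with HA.

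**Step 4. Which components conflict.**

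| Component in 2.11 | Limited loading of the leg (2.9) | Light activity (2.9) |
|---|---|---|
| Warm-up | compatible | compatible |
| Wall squats | conflicts | conflicts |
| Seated chair work, unloaded | compatible | compatible |
| Seated chair work with added weight | not clearly covered | may conflict |

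**Step 5. Does a 48 h rule fit?** With injection on day 1 at 0 h, day 3 is 48 h, day 5 is 96 h and day 7 is 144 h. The next injection is on day 8, at 168 h. Three sessions a week fit.

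**The case against.** The strongest reply is that 2.9 gives graded advice. It limits loading without forbidding it, and a therapist supervises the training. A sensible therapist could keep the first session light and offend neither section, and a treatment manual that is not shown may say so. This softens the conflict but does not remove it. Section 2.11 prescribes the squats from the start and ties load to strength, and no part of the article exempts hours 24 to 48. Both rules are printed, so this is not a detail that the article leaves out.

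It can also be said that the weight-training sentence follows the chair exercise, so it describes resistance while seated and not body weight on the leg. That stands: the firm part of the point is the squats.

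For HA, the shared method and similar guidance probably carry the advice across. That also stands, and the sentence proposed for 2.10 only makes it explicit.

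Finally, section 2.17 says that recruitment and intervention are already in progress, so a change alters an exercise schedule in use. That is a real cost, though a small one, and it falls on both arms alike.

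A reader might take the squat duration as applying to each squat, which gives at least 5 × 2 = 10 minutes of squatting in the disputed session. The protocol's own timings do not support this. Six chair groups with 2-minute rests between them use 5 × 2 = 10 minutes for rest. Together these fill the 20-minute session and leave no time for the chair repetitions.

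**Conclusion.** The contradiction is real and minor. The start rule fixes one 24-hour window of conflicting instructions per participant, clear for the wall squats and less clear for seated resistance. Up to four windows per participant are permitted. The count is explicit for the 35 PRP participants and probable for all 70. It assumes that two days means 48 hours and that injections are exactly a week apart.

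Two stronger conclusions might be inferred, and neither is supported. The first is that every participant trains against the aftercare advice four times. The text forces no session into the windows after injections 2 to 4; it only fails to prevent one. The second is that the conflict biases the comparison of PRP with HA or weakens the trial's power. Training is the same in both arms, the aftercare is probably the same too, and nothing in the article links this window to the outcomes. The point concerns consistent participant protection only.

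**What to change.** In 2.11, hold wall squats and loaded chair work until at least 48 hours after each of the four injections, for example by placing sessions on days 3, 5 and 7 of each injection week. Allow the warm-up and unloaded seated work from 24 hours. In 2.10, state that the two-day aftercare of 2.9 applies to the HA group as well.

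The cost is rewording in two sections. The first squat or loaded session moves by up to 24 hours, three sessions a week still fit, and no visit, staff or procedure is added. There is less freedom in choosing training days during the four injection weeks. As the trial is under way, earlier and later participants would differ slightly in training timing, so the change should be dated and applied to both arms together.

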### 2.12. Primary Outcome

VAS score [22]: the VAS score is used to assess knee joint pain. It is usually a flat line, 100 mm in length, anchored by word descriptors at each end. Patients mark the point on the line of current pain. The VAS score is then decided by measuring in millimeters from the left end of the line to the point that the patient marked. Patients can experience pain ranging from no pain to extreme pain. The higher the score, the severer the pain. The VAS score is measured during all the assessment visits.Western Ontario and McMaster University Bone joint Index (WOMAC) Scoring System [23]: the WOMAC scale specifically includes 24 questions in three aspects of joint pain, stiffness, and functional limitation. Each question consists of five levels of pain: none, mild, moderate, severe, and very severe. The lowest score for WOMAC is 0, and the highest score is 96 for each item. The higher the score, the worse the joint function.

Variations in VAS scores and WOMAC functional scores for each patient are compared and analyzed at specified time points between groups along with the comparison of the average scores among groups.

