## 2. Methods

### 2.1. Study Design and Setting

This is a prospective randomized controlled superiority clinical trial to assess the adequacy and security of intra-articular injection of PRP and intra-articular injection of HA for knee osteoarthritis. This overview was conducted at the General Hospital of Ningxia Medical University. A total of 70 participants with knee osteoarthritis are being randomly allocated to the PRP and HA groups at a 1 : 1 ratio. Prior to initiation of the study, all subjects complete daily activity tests after a questionnaire asking for detailed medical history. All study participants are required to sign a written informed consent prior to participation. The study includes assessments at the following time points: before intervention, 1 month after intervention, and after a further follow-up period of 3 and 6 months with no active intervention (Figure 1).

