### 2.2. Sample Size Calculation

In this strategy, WOMAC pain score reduction was concluded to be the most relevant indicator based on a previous study conducted by Vaquerizo et al. [21].

The test measure was evaluated using PAS 24.0 criteria, and the total number was set at 70 cases, specifically 35 cases in each group (permitting 20% dropout rate). The power is 80%, and the level of significance is 0.05. The overall sample size is anticipated to be 70 patients (35 in each group) (Table 1).

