### 2.15. Statistical Analysis

The SPSS 26.0 software is used for data analysis. All quantitative data are indicated by the percentile calculator. The chi-square test is used if the measurement data are normally distributed, and the data are expressed as mean ± standard deviation. The independent sample *T*-test is utilized to compare the mean values of the two groups. If the measurement information does not adjust to the normal distribution, the interquartile spacing is described and the independent sample Mann-Whitney *U* test is utilized. To assess changes within and between groups, we perform an analysis of variance (ANOVA) on repeated measures. Intentionality analysis and multiple interpolation are used to complete the missing values, and intentionality analysis and conforming protocol analysis are used to determine the sensitivity of the inflammatory outcome efficacy indicators. Statistical significance is assumed *P* less than 0.05.

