## Figures and Tables

**Figure 1 fig1:**
[figure not shown]
The planned flowchart of the trail. PRP: platelet-rich plasma; HA: hyaluronic acid; HE: health education; QT: quadriceps femoral training; VAS: Visual Analogue Scale; WOMAC: Western Ontario and McMaster University Bone joint Index; ADL: activity of daily living score; ESR: erythrocyte sedimentation rate; CRP: C-reactive protein; IL-6: interleukin-6; X-ray: X-ray examination.

**Table 1 tab1:** Schedule outlining the enrolment, interventions, and assessments for the proposed randomized controlled trial.

Timepoint	Study peroid				
	Enrollment	Intervention period 1-4 (weeks)	Outcome assessment 4 (weeks)	Outcome assessment 12 (weeks)	Outcome assessment 24 (weeks)
Inclusion criteria	×				
Exclusion criteria	×				
Informed consent	×				
Baseline	×				
Randomization and allocation	×				
Intervention		×			
VAS	×		×	×	×
WOMAC	×		×	×	×
ADL	×		×	×	×
ESR	×		×	×	×
CRP	×		×	×	×
IL-6	×		×	×	×
TNF-*α*	×		×	×	×
X-ray	×		×	×	×
Adverse events		×	×	×	×
Reasons of dropout and withdrawals		×	×	×	×

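### VAS and WOMAC are both primary and are compared at three visits at an unadjusted 0.05, but no visit, success rule or test is named as deciding superiority

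*Protocol article*

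**What the plan says.** - **Two primary outcomes, not ranked.** The Abstract states: "The primary outcomes are measured using the Western Ontario and McMaster Universities Osteoarthritis Index (WOMAC) and the visual analog scale (VAS". Section 2.12 lists the same two.
- **Compared at several visits.** Section 2.12: "Variations in VAS scores and WOMAC functional scores for each patient are compared and analyzed at specified time points between groups". The same sentence adds that mean scores are compared too. Section 2.1 gives the assessments as "before intervention, 1 month after intervention, and after a further follow-up period of 3 and 6 months with no active intervention". Table 1 has three post-baseline assessments, at weeks 4, 12 and 24, with VAS and WOMAC marked at each.
- **One flat threshold.** Section 2.15: "Statistical significance is assumed *P* less than 0.05". It does not say whether tests are one- or two-sided.
- **More than one test, none ranked.** Section 2.15 plans an independent t-test, or Mann-Whitney U for non-normal data, and also a repeated-measures ANOVA for changes within and between groups.
- **Sample size on a third version of WOMAC.** Section 2.2: "WOMAC pain score reduction was concluded to be the most relevant indicator based on a previous study", with no visit attached, and then "The power is 80%, and the level of significance is 0.05". Section 2.12 describes the 24-item index and also refers to WOMAC functional scores.
- Section 2.1 calls the trial a superiority trial.

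**The concern.** A superiority trial needs one decision rule to which its significance level applies. Here two outcomes at three visits make six between-group comparisons, each read against 0.05, and nothing says which of them, or what combination, establishes that PRP is superior to HA. As the text stands, superiority could be claimed on whichever outcome and visit crosses the threshold. The 0.05 and the 80% in section 2.2 describe a single comparison, and the article never identifies it. The sizing sentence does not fill the gap: WOMAC pain is not listed as a primary outcome in its own right, and no visit is given for it.

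**Working it through.** **The plan's own figure.** Section 2.2 gives 70 patients (35 per group), 80% power, 0.05 and 20% dropout, but no effect size or SD, so the number can only be back-solved.
- Evaluable per group: 35 × 0.80 = 28.
- n per group = 2(1.960 + 0.842)²/d². With d = 0.75 this is 27.9, so 28, and 28/0.80 = 35.

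The stated 70 is therefore coherent for one two-sided comparison at 0.05 with a standardised difference of about 0.75. That d is implied, not stated.

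**Inputs for the error rate.** Two outcomes (section 2.12) × three visits (Table 1) = six comparisons, each at 0.05 (section 2.15). Two-sided testing is assumed. The documents give no correlation between VAS and WOMAC or between visits, so a range is shown.

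**Rule A: any one of six counts as success.** If independent, 1 − 0.95⁶ = 0.265. For correlated tests, six null z-statistics were simulated and the proportion with at least one |z| > 1.96 was counted. In the product model, the correlation between two tests is the outcome correlation times the visit correlation where both differ. In the common model, every pair has the same correlation.

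| Assumed correlation | Product model | Common correlation |
|---|---|---|
| 0 | 26.5% | 26.5% |
| 0.5 | 22.0% | 20.8% |
| 0.7 | 17.6% | 16.4% |
| 0.8 | 15% | 13.9% |
| 0.9 | 11.5% | 10.9% |

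These figures count false positives in either direction. For a false finding in favour of PRP only, independence gives 1 − 0.975⁶ = 14.1%. The product model gives about 11% at 0.5 and about 6% at 0.9. Each is roughly half the two-sided figure, against a nominal 2.5%.

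**Rule B: one overall repeated-measures test per outcome, either may succeed.** Two tests give 1 − 0.95² = 9.75% if independent, 9.1% at correlation 0.5, 7.8% at 0.8 and 7.0% at 0.9.

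**Rule C: both outcomes must be significant, at one named visit or with one overall test each.** The rate cannot exceed 5%. With no effect on either outcome it is 0.3% under independence and 2.2% at correlation 0.8.

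**Effect on power** (28 evaluable per group, d = 0.75 on each outcome, t-test):

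| Rule | Power |
|---|---|
| One comparison at 0.05 | about 79% |
| One outcome at 0.025 (first step of Holm over two) | about 69% |
| One outcome at 0.05/6 = 0.0083 | about 53% |
| Both must be significant at 0.05 (normal approximation) | about 64% if independent, 69% at correlation 0.5, 73% at 0.8 |

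The single-comparison figure is 79% rather than 80% because it uses the t distribution.

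**The case against.** A reader might infer that the trial simply has a false-positive rate in the region of 16-27%. The documents do not support a fixed figure, for four reasons.

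- **No success rule is stated.** Section 2.15 gives a threshold for significance, not a rule for success. Any-one-of-six is one reading; both-must-win would keep the rate at or below 5%.
- **A repeated-measures ANOVA is planned.** If it supplies the between-group test, there are two tests rather than six, and the rate is about 7-10%.
- **No correlations are given.** A lower limit of 16% needs correlations of about 0.7; at 0.9 the figure is near 11%. The independent value, 26.5%, is an upper reference.
- **The figure covers only six primary comparisons, in both directions.** It is not a rate for the whole trial, and the chance of a false claim for PRP specifically is about half of it. The comparison of average scores in section 2.12 may just mean comparing group means, so it cannot be counted as extra tests.

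It is also fair that an adjustment procedure is often left to a statistical analysis plan, which is not shown here, so its absence alone is not the finding.

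What survives is the core. Which measure, at which visit, by which test decides superiority is the definition of the primary endpoint and belongs in the protocol. The article also goes beyond silence: it sets out comparisons of two primary outcomes across visits at a flat 0.05. Reading the ANOVA as decisive does not settle the matter, because section 2.15 does not rank it above the other tests and two unadjusted outcomes still exceed 5%. Reading both-must-win into the text repairs the error rate but not the stated 80% power.

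**Conclusion.** The concern holds as a missing decision rule. The two-sided chance of at least one false positive on the primary outcomes depends on a rule the article leaves open:

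- about 26% (independent), or about 11-22% (assumed correlations 0.9 to 0.5), if any one of six comparisons suffices;
- about 7-10% if each outcome has one overall repeated-measures test and either may succeed;
- at most 5% only if both must succeed, at one visit or with one overall test each.

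The arithmetic under each rule is firm; the correlations and two-sided testing are assumptions. The stated 0.05 and 80% fit one comparison, and the article does not say which. An either-may-win rule breaks the 0.05, while both-must-win or an alpha split lowers the power.

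**What to change.** Before unblinding, and without sight of results by group, amend sections 2.12 and 2.15:

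1. Name one primary measure, one visit and one test at two-sided 0.05. WOMAC pain is a natural candidate because it sized the trial, but the text does not dictate it, and no visit is favoured by section 2.2. The sponsor should choose and justify both.
2. Test the other outcome and the other visits in a stated fixed order, or label them supportive.
3. If VAS and WOMAC both stay primary, test them at that one visit with Holm, or state that both must be significant.
4. Say which WOMAC score is meant, and make sections 2.2 and 2.12 agree.

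**Cost.** Amended text in these sections and a registry update; no extra patients or data for the single-comparison option. Results outside the named comparison become secondary. Keeping both outcomes primary costs power: about 69% at 0.025 against 79% at 0.05 (28 evaluable per group, back-solved d of 0.75), or about 64-73% if both must succeed. In that case the stated 80% has to be restated. Section 2.17 reports recruitment and intervention under way, so the amendment should be dated and its reason recorded.
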